**Trial Registration:**

CTRI/2023/03/051064; https://tinyurl.com/2xdus53j

**International Registered Report Identifier (IRRID):**

DERR1-10.2196/59018

## Introduction

### Background

Parkinson disease (PD) is the second most common neurodegenerative disease, with over 10 million people worldwide having PD [1]. PD is highly prevalent in Asia, with a frequency of 70 patients with PD per 100,000 people in India [2,3]. PD is a progressive, multidimensional disorder characterized by the degeneration of dopaminergic neurons, resulting primarily in motor dysfunctions including bradykinesia, rigidity, tremors, and postural instability [4]. PD can also result in concurrent nonmotor manifestations including psychiatric and mood-related alterations such as apathy, depression, and anxiety [5,6]. Cognitive involvement is prevalent as well, with a high occurrence of slow processing speed and deficits in learning and attention in patients with PD [7,8]. They are also seen to experience behavior disturbances [9].

Previous research suggests that medical or surgical treatments do not change the progression of PD [10]. It is seen that alternative therapies such as music, dance, and mindfulness might help delay the progression of PD symptomatology while improving the quality of life (QoL) [11,12]. In addition, therapies such as exercise and aerobic dance can have neuroprotective effects led by neuroplasticity [13]. Exercise is further seen to modulate dopamine neurotransmission [14].

### Music Therapy

It has been observed that music modulates the brain regions related to movement, behavior, and cognitive processes [15]. Musical rhythm offers time-based groupings of sounds that provide auditory cueing and signaling strategies. This can help in restoring internal synchronization mechanisms and enable easier control of motor rhythmicity [15]. Evidence suggests that music exposure can enhance balance and functional mobility in patients with PD [13]. Listening to different musical genres has also been shown to induce spatiotemporal sense and trunk oscillations in the gait of patients with PD [16]. The music further activates the amygdala-related pathways and is seen to reduce depression and elevate mood in patients with PD [17]. Abell et al [18] conducted a study demonstrating that choral singing for a minimum of 6 months led to improvement in both motor and non-motor symptoms in patients with PD.

### Dance Therapy

Dance therapy uses sensory-motor methods such as visual and spatial focus to facilitate improvement in one’s physical and mental health [11]. Dancing entails the practice of movements, postures, and body control, which might address bradykinesia, postural instability, and rigidity associated with PD [19]. McNeely et al [20] conducted a 2-year longitudinal study, wherein significant improvements in motor measures were observed in weekly tango dance sessions, reflected through the assessments of the outcome measures at 12 and 24 months. Dance is also seen to enhance mood, socialization, self-esteem, and QoL in patients with PD [21]. Additionally, high levels of commitment are observed in training programs offering American tango versus traditional exercise [22]. Dance programs among patients with PD can further improve the QoL of caretakers [22].

Certain dance forms and particular cultural dances are seen to have varied influences on PD symptoms [23,24]. For instance, a study claims that ball dancing might be more effective than tango [23]. Furthermore, there is evidence that Amazonian dances have distinct cultural peculiarities such as knee flexion and accentuated hip movements that can improve PD motor symptoms [24]. However, there is limited research on the effect of Indian art forms on PD symptomology and progression.

### Meditation

Meditation is a mental state of quiescence that affects the body's functioning and helps patients gain attentional control and maintain focus on their intentions rather than being controlled by external environmental factors [25,26]. Mindfulness meditation stimulates the parasympathetic nervous system of the body through deep breathing exercises and positively impacts concentration and emotion regulation [27]. A mindfulness meditation research study conducted in South Korea, among patients with depression, anxiety disorders, and drug abuse, showed that meditation has positive effects on emotional and psychological stability, depression, anxiety, and memory loss [28].

Most of the studies to date have either been conducted over a short duration of time or on a small group of patients or have evaluated limited parameters. There has been no comprehensive review exploring the effect of dance or music and meditation on QoL, and limited studies take the QoL of caretakers into consideration. Additionally, there is limited research on the effectiveness of alternative therapies on the Indian population. This study aims to evaluate the effectiveness of music or dance and meditation on QoL and the progression of symptoms in patients with PD.

## Methods

### Study Design

The study is a single-blinded, longitudinal, randomized controlled trial (RCT) that will take place over a 6-month time period at Jaslok Hospital and Research Center, Mumbai, India. Participants will be randomly allocated into 2 groups: the control and intervention groups, having 15 participants in each arm. The intervention group will be further divided into dance or music as per the participant’s choice. The CONSORT (Consolidated Standards of Reporting Trial) flowchart summarizes the enrollment and allocation of the participants (Figure 1).

**Figure 1 figure1:**
[figure not shown]
CONSORT (Consolidated Standards of Reporting Trial) flowchart summarizing the format of the study. PD: Parkinson disease.

### Aims

#### Primary End Point

The primary end point is to examine the effect of dance or music and meditation on the progression of mild and moderate PD using the Unified Parkinson’s Disease Rating Scale (UPDRS) I-III and Parkinson’s Disease Questionnaire-39 (PDQ-39) scores in patients with PD.

#### Secondary End Point

The secondary end points include the following.

Detecting the impact of these therapies on cognition, mood, and behavior through neuropsychological batteries.Assessing the impact on the QoL of the caregivers of patients with PD.

### Participants

#### Inclusion Criteria

The inclusion criteria are as follows:

Patients with a confirmed diagnosis of mild to moderate PD (motor UPDRS III score of 43 or below)Patients should be residents of Mumbai (the city where the research is conducted)All patients should be physically able to take part in the activities

#### Exclusion Criteria

The exclusion criteria are as follows:

Patients with advanced PDParticipants with extreme balance-related problems or the inability to moveAge >80 yearsPatients with other movement-related disorders such as atypical Parkinsonism and essential tremorsPatients who underwent deep brain stimulationAll patients with secondary ParkinsonismPatients with a history of falls

### Randomization

Eligible participants will be randomized into the intervention and control groups through a randomized allocation sequence devised by an independent statistician.

### Blinding

This is a single-blinded study, as the assessors measuring the outcomes will be blinded to the allocation of groups.

### Assessments

All assessments will be conducted during the “on phase,” that is, during the phase when the PD medication is in effect. The outcomes will be assessed by a specialist nurse, a neuro-consultant, and a consultant psychologist. The neuro-consultant is a functional neurosurgeon with pioneering work in this field and more than 30 years of experience in movement disorder surgeries. The specialist nurse has been involved in the treatment of movement disorder patients for more than 26 years and is a certified UPDRS assessor. For the reassessments, the marker who conducted the initial assessment will conduct subsequent assessments.

### Attrition and Missing Data

Due to the long duration of the study, it is expected that there will be a moderate attrition rate. To reduce the attrition rate and maintain commitment to the project, the importance of complete participation and consistency during the sessions will be conveyed to the team members and participants. The reassessments will be arranged at the participants’ convenience to minimize the possibility of missing data.

### Intervention Group

The patients will be given the option to choose from dance and music modalities. Meditation will be provided in every session. Active engagement for therapy is required for up to 6 months. All the activities will be improvised as per the abilities of the patients. The duration of each class will be around 1 hour. Both music and dance modalities follow a similar structure. All the classes will be followed by a 3-part format.

Part 1: Classes will begin with 10 minutes of warm-up activities that will cover a wide range of stretching and hand-leg-eye coordination exercises.Part 2: The 45-minute dance or music sessions will follow a different format during this stage.Part 3: The sessions will conclude with 15 minutes of guided meditation.

The dance sessions will begin with warm-up activities with a focus on Indian classical dance steps. The classical dance focuses on gait and balance-related tasks, intending to reduce bradykinesia, shuffling gait, and the tendency to freeze in PD [29]. Classical dances emphasize greatly on hand-motor coordination and eye movement [29,30]. The eye-movement exercises might further improve lower gaze palsy in patients with PD. Alongside this, the patients will be engaged in the dance form of their choice. They will be offered various options of dance forms such as Bollywood dance, group dance, and garba. Patients can follow the choreography of the dance invigilator or perform freestyle. Following this provided that every session has at least 2 couples, the patients will practice waltz for 10 minutes.

Meanwhile, in the music sessions, the patients will engage in vocal exercises and will be given the choice of playing a musical instrument; singing the karaoke; or auditory stimulation, that is, listening to the karaoke. They will be encouraged to actively participate in the sessions.

The meditation will be administered by a professional trained in conducting meditation classes for the general population. Participants will be asked to close their eyes and sit in a relaxed posture either cross-legged or on a chair. Hands will be on knees with palms open. The mindfulness meditation will include guided instructions for deep breathing followed by a body scan and then guided instructions to pay attention to their thoughts and feelings.

All participants will be instructed to follow their daily routine and normal medication schedule. They will be instructed to keep the program coordinator informed if they make any significant changes to their treatment or their medication dosage or schedule. The participants in the intervention group will be asked to commit to the program and to take part in music or dance and meditation sessions thrice, weekly, for 6 months. On a weekly basis, patients should attend at least 1 session in physical presence, while the other sessions will be monitored through videoconferencing and home-based logs.

The patients will also be provided with the recordings of videos with instructions and a breakdown of each activity taught during the face-to-face sessions, making it easier for the participants to practice at home. A complete audio of the guided meditation schedule will be shared with the patients as well. The patients will be instructed to maintain an activity logbook documenting their adherence to home-based practice. Class attendance will be monitored and documented.

### Control Group

Participants in the control group will be instructed to continue their regular activities and medication during the study period. They will be offered the chance to enroll in the dance or music sessions after the completion of the study. During the study, the patients from the control group will not interact with participants in the intervention group.

### Reassessments

Reassessments for all participants will take place within 6 months of allocation (this is a deviation from the originally submitted protocol, which had assessments at 2 time points: 3 and 6 months. The deviation was incorporated considering the fact that major changes were likely to be noted in only at 6 months).

### Outcomes Measures

#### Primary Measures

##### Progression of PD Symptoms

The UPDRS I-III consists of 31 items assessing the severity of nonmotor and motor aspects of daily living and motor examination [31]. The responses will be scored from 0=no impairment to 4=severe impairment. Higher scores indicate higher severity (maximum score=124). This measure has demonstrated a strong internal consistency with α=0.96 and high concurrent validity against other similar constructs [31].

##### Quality of Life

The PDQ-39 is a 39-item self-report measure that measures the functional impairments in the following modalities: Parkinsonism symptoms, systemic symptoms, and emotional and social functioning [32]. Each item will be scored on a categorical scale from 0=never to 4=often. A summary index is further calculated ranging from 0 to 100. Higher scores indicate worse QoL. The PDQ-39 is widely used with good internal consistency of α=0.72-0.93 [33] and good concurrent validity against the Hoehn and Yahr Index and other similar constructs (0>0.60) [34].

#### Secondary Measures

##### Mood

The Beck Depression Inventory is a 21-item measure that is used worldwide to assess the severity of depression [35]. The items can be grouped into distinct symptoms of depression: cognitive, somatic, affective, and vegetative symptoms. This scale has a strong internal consistency of 0.88 and strong concurrent reliability with the depression subscale of the Symptom Checklist-90-R [36].

Additionally, the Parkinson Anxiety Scale is a 12-item measure that assesses 3 categories of anxiety: persistent anxiety, episodic anxiety, and avoidance behavior [37]. Each item will be scored on a categorical scale from 0=never to 5=often. Higher scores indicate worse anxiety (maximum score=63). This measure has a strong internal consistency of α=0.87-0.89 and good known-group and convergent validity [37].

##### Balance and Mobility

The timed up and go (TUG) and Berg Balance Test (BBT) assess mobility and risk of falls. The TUG is an observational test testing the gait, style, and time taken for the participant to get up from a chair, move for 3 meters, turn around, and return to the seat [38]. The TUG is seen to have good retest and interrater reliability in patients with PD [39]. Additionally, the BBT is an assessor-rated scale that records mobility through 14 tasks, with their performance being rated on a 5-point scale ranging from 0=poor performance to 4=good performance [40]. The BBT has a good internal consistency of α=0.93 and strong concurrent validity as strongly correlated with the Mini Balance Evaluation Systems Test [41].

##### Caregiver Scale

The Zarit Burden Interview is a 29-item self-report measure assessing the burden of the caregiver, measuring the psychological well-being, financial, and overall burden [42]. Each item is to be scored from 0=never to 4=always. The Zarit Burden Interview has good reliability with α=0.89-0.95 and good external validity with PD-related carer scales [42]. The Parkinson’s Disease Questionnaire-Carer is a 29-item measure further assessing the mood, social life, and relationships of the caregiver with a good test-retest reliability [43]. This scale will be rated from 0=never and 4=always. Higher scores indicate worse QoL (maximum score=100).

##### Cognition Scale

The Mini-Mental State Examination evaluates performance at various cognitive components including orientation, attention, and recall [44]. A higher score signifies better cognitive abilities (maximum score=30). This measure has good test-retest reliability (0.80-0.95) and satisfactory construct validity against various gold standards used to diagnose cognitive impairment [44].

##### Behavioral Disorders

The Questionnaire for Impulsive-Compulsive Disorders in Parkinson’s Disease Rating Scale is a 28-item scale that records impulsions, compulsions, and compulsive medication usage [45]. Responses will be recorded on a 5-point Likert scale with 0=Never and 4=Often. This measure demonstrated high sensitivity and specificity across all subscales [45].

### Data Analysis

IBM SPSS software will be used for the statistical analysis. Descriptive statistics will summarize the demographics, health conditions, and clinical outcomes at all 3 time points. Categorical variables including the Likert rating scales will be expressed in percentages and frequencies. The median and mode will also be ascertained for these data. Additionally, chi-square tests will be conducted, and *P* values will be ascertained to decipher the difference between the 2 groups against each outcome variable throughout the 3 time points.

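### Chi-square is the only between-group test stated for every outcome, although both primary outcomes and TUG time are numeric; at 15 v 13 patients it loses most or all of the power

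*Protocol article*

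**What the plan says.** The Data Analysis section of the protocol article classes rating scales as categorical: "Categorical variables including the Likert rating scales will be expressed in percentages and frequencies". It continues: "The median and mode will also be ascertained for these data. Additionally, chi-square tests will be conducted". The purpose of the test is "to decipher the difference between the 2 groups against each outcome variable throughout the 3 time points". No other inferential method is named, and no cut-point or grouping of scores is given.

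The outcomes that this test must serve are defined elsewhere in the article:

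- The Primary End Point section assesses progression "using the Unified Parkinson’s Disease Rating Scale (UPDRS) I-III and Parkinson’s Disease Questionnaire-39 (PDQ-39) scores in patients with PD".
- UPDRS I-III has 31 items scored 0 to 4: "Higher scores indicate higher severity (maximum score=124".
- For PDQ-39: "A summary index is further calculated ranging from 0 to 100".
- TUG includes the "time taken for the participant to get up from a chair", walk 3 metres, turn and return.

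The Assessments section has the same rater carry out the initial and later assessments, so a pre-treatment value exists. The Reassessments section keeps one follow-up at 6 months and drops the 3-month visit. The Results section reports 28 completers, 15 intervention and 13 control.

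**The concern.** A Pearson chi-square on a group-by-score table treats scores as unordered labels. Relabelling or shuffling the score categories leaves the statistic unchanged, so a score of 20 is no closer to 21 than to 90. It therefore ignores by how much, and in what order, the arms differ. It also makes no use of the baseline score, although the trial's question is progression. With 28 patients spread over many values, the expected counts are too small to support the chi-square approximation. The stated inferential output is a P value, which does not say how large an effect is.

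This is the only stated comparison for both primary outcomes. If it is run on the totals, a real benefit would almost certainly be missed. If the scores are grouped first, a moderate or large benefit would more often be missed than found.

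**Working it through.** **Inputs from the article.** 28 completers, 15 v 13 (Results); UPDRS I-III from 0 to 124, PDQ-39 index from 0 to 100, TUG time (Outcomes Measures); chi-square for each outcome (Data Analysis). The article states no sample-size calculation, alpha, SD or effect size, so there is no power figure to reproduce. Its completer shares do reproduce: 15/28 = 53.6% and 13/28 = 46.4%, stated as 54% and 46%.

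**Step 1. All values distinct (no assumption on SD or effect).** Each score is a column holding one patient, with expected counts 15/28 = 0.54 and 13/28 = 0.46.

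- A column with an intervention patient contributes (1 − 15/28)²/(15/28) + (13/28)²/(13/28) = 13/15.
- A column with a control patient contributes 15/13 by the same algebra.
- Total: 15 × 13/15 + 13 × 15/13 = 13 + 15 = 28, on 28 − 1 = 27 df, so P = 0.41.

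The sum does not depend on which patient has which score. Two extreme data sets confirm this:

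| Data | Chi-square P | t-test P | Mann-Whitney P |
|---|---|---|---|
| Arms completely separated | 0.41 | 3 × 10⁻⁹ | 8 × 10⁻⁶ |
| Arms interleaved | 0.41 | 0.38 | not computed |

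With all 30 patients (30 on 29 df), P is again 0.41.

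**Step 2. Expected counts if scores fall into k equally used levels (15/k and 13/k).**

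| k | Intervention | Control |
|---|---|---|
| 5 | 3.0 | 2.6 |
| 4 | 3.75 | 3.25 |
| 3 | 5.0 | 4.3 |
| 2 | 7.5 | 6.5 |

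Only a two-way split puts every expected count above the usual threshold of 5.

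**Step 3. Power by simulation.** Assumptions, none from the article: normal scores rounded to integers, two-sided 5%, SD 8 or 15, baseline to 6-month correlation 0.7 (0.5 to 0.8 as a range), 5,000 runs per setting, 15 v 13. On average about 18 to 19 distinct scores occur at SD 8 and about 22 to 23 at SD 15. Ranges below are across the two SDs.

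| True difference | Chi-square, raw totals | Chi-square, quartiles | Chi-square, median split | t-test | ANCOVA, r = 0.7 |
|---|---|---|---|---|---|
| 0 | about 0% | 4.5–4.8% | 3.0–3.6% | 4.6–4.7% | 4.7–5.0% |
| 0.5 SD | about 0% | 14–15% | 13–14% | 24–25% | 42% |
| 0.8 SD | about 0% | 29–31% | 30–31% | 52–53% | 78–80% |
| 1.0 SD | about 0% | 46% | 44–46% | 72–73% | 94% |

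For correlations of 0.5 to 0.8, ANCOVA power at 0.8 SD runs from about 63–65% to 91%. The first row shows no inflation of type I error for any of the chi-square versions.

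**The case against.** The strongest reply is that a condensed article may leave detail to an analysis plan that is not shown. That covers what is merely unsaid, such as baseline adjustment or confidence intervals, and these are not counted here as separate defects. It does not cover the test, which the article states and applies to every outcome. A plan using another test would contradict this text, and the text would still need correcting.

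Second, the article does not say how scores enter the table. The reference to Likert scales could mean single items or bands. This stands, and it limits the claim: the complete loss of power applies to ungrouped totals only. Grouping leaves some power, but well below that of a t-test.

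Three stronger readings are tempting, and the documents do not support them:

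- *That the test is invalid in the sense of producing false positives.* Rejection under no effect stays at or below about 5%. The approximation is unsupported, but the demonstrated harm is lost power.
- *That the trial will yield no means or SDs for planning a later trial.* The section promises descriptive statistics for clinical outcomes. The sentence on median and mode concerns categorical data, and nothing excludes means and SDs for totals.
- *That visits will be pooled in one table, so that patients are counted more than once.* The article describes no such pooling.

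Finally, the preference for ANCOVA over a t-test or rank test rests partly on an assumed correlation. That affects the size of the gain, not the case against chi-square.

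**Conclusion.** The point holds as a wrongly fixed method. Two findings need no assumption about SD or effect: with 28 distinct values the test returns P = 0.41 for any data, and expected counts are about 0.5 per cell on distinct values and about 3 on an evenly used 5-level item.

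The power comparison is illustrative. At 0.8 SD it is about 0% on raw totals and about 30% on quartiles or a median split, against about 53% for a t-test and 79% for ANCOVA at an assumed correlation of 0.7. A reader might infer that any null result would be due to the test rather than the intervention. That does not follow if scores are grouped, but a null result from this test would be weak evidence of no effect. Because this is the only stated comparison for both primary outcomes, it should be corrected before results are reported.

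**What to change.** In the Data Analysis section:

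1. For all scale totals and TUG time, replace chi-square with ANCOVA of the 6-month score on allocated group and baseline score. Report the adjusted mean difference with its 95% CI. Support it with a rank-based or permutation test, because n is small.
2. Keep chi-square or Fisher's exact test only for outcomes that are truly categorical. Describe baseline variables without significance tests.
3. Bring the two mentions of 3 time points into line with the Reassessments section, which drops the 3-month visit.
4. Record the date of the change relative to any unblinded look at the data, because the Results section says that analysis is under way.

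The cost is a few lines of analysis code and a documented change to the plan. Both scores are already collected, so no new data are needed.

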## Results

The data collection for this paper commenced in February 2023 and was completed in February 2024. A total of 30 participants were recruited, of which 28 completed the study (intervention group: n=15, 54% and control group: n=13, 46%). The data are currently being analyzed, and the final results are anticipated to be published in December 2024.

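### The Data Analysis section plans summaries and tests at 3 time points, but the current schedule implies two, only one of them after allocation

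*Protocol article*

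**What the plan says.** Three sections of the protocol article bear on the number of assessments.

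- **Assessments.** There is an initial assessment, and the same rater sees the participant again: "the marker who conducted the initial assessment will conduct subsequent assessments".
- **Reassessments.** The current rule is that "Reassessments for all participants will take place within 6 months of allocation". The article adds that "this is a deviation from the originally submitted protocol, which had assessments at 2 time points: 3 and 6 months". The reason given is that "major changes were likely to be noted in only at 6 months".
- **Data Analysis.** Descriptive statistics are to cover "clinical outcomes at all 3 time points", and chi-square tests with P values are to examine the "difference between the 2 groups against each outcome variable throughout the 3 time points".

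No section names a third assessment under the current schedule. On timing, the Results section reports that data collection is complete and that "The data are currently being analyzed".

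**The concern.** The schedule and the analysis are both current text, and they disagree. The Reassessments section records a change of design, while the Data Analysis section still carries the count from before the change, twice.

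Three things are at stake.

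- A reader cannot tell which time points the analysis covers. Taken literally, the text plans a summary and a test at a visit that the current schedule no longer contains.
- The text treats baseline as a testing occasion like any other. Allocation is random, so a between-group difference at the initial assessment arises by chance. Its P value says something about the randomisation and nothing about dance, music or meditation.
- Separate tests at each time point invite a weak inference: no significant difference at baseline, a significant one later, hence an effect. The direct question is whether the groups differ at 6 months given where they started. The baseline scores that this comparison needs are already part of the design.

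The article is the public reference against which the results will be read, so the analysis text should match the design before those results appear.

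**Working it through.** No power or error-rate formula applies here. The check is a count.

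**Inputs**

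- Initial assessment: 1 (Assessments section). I take this to be the baseline.
- Reassessments in the superseded schedule: 2, at months 3 and 6 (Reassessments section: "which had assessments at 2 time points: 3 and 6 months").
- Reassessments in the current schedule: 1. This is inferred from the stated deviation and its reason.
- Time points in the analysis: 3 (Data Analysis section, stated twice).

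**Formula:** time points = initial assessments + reassessments.

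1. *Reproducing the plan's figure.* Superseded schedule: 1 + 2 = 3. This matches the Data Analysis section.
2. *Current schedule.* 1 + 1 = 2. This does not match.
3. *Difference.* 3 − 2 = 1. The time point in excess is month 3.
4. *Comparisons after allocation, per outcome.* Superseded schedule: 3 − 1 = 2. Current schedule: 2 − 1 = 1.

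For each outcome, the three planned time points therefore divide as follows.

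| Planned time point | In current schedule? | What a between-group test there shows |
|---|---|---|
| Baseline | Yes | The randomisation only |
| Month 3 | No, by inference | Nothing; no visit is scheduled |
| Month 6 | Yes | The effect of the intervention |

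**Illustration of scale.** The Outcomes Measures section describes 10 instruments: UPDRS I-III, PDQ-39, Beck Depression Inventory, Parkinson Anxiety Scale, timed up and go, Berg Balance Test, Zarit Burden Interview, Parkinson's Disease Questionnaire-Carer, Mini-Mental State Examination and the impulsive-compulsive disorders scale. Assume one test per instrument per time point, which the article does not state. The text then describes 10 × 3 = 30 tests: 10 at baseline, 10 at month 3 without a scheduled visit, and 10 at month 6 that bear on effect.

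**The case against.** The strongest reply is that this is a wording slip. The authors changed the schedule, disclosed the change, and did not update a number in another section. If only one visit after baseline remains, the time of the primary comparison follows from the design, and nothing shows that the 6-month comparison is harmed. Most of this stands. It limits the point to a correction of text, but it does not remove the conflict, because the outdated count governs both the summaries and the tests.

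A second reply is that the article never says in so many words that the 3-month visit was dropped. It also uses plural words for the later assessments. That is correct. Dropping month 3 is an inference, although it is the only reading that makes sense of calling the new schedule a deviation and giving the 6-month reason for it. It is also why the article should state whether 3-month data exist.

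A third reply is that baseline adjustment is a choice of estimator that a full protocol or statistical analysis plan may settle, and that neither document is shown. The adjustment is indeed not needed to prove the mismatch. It belongs in the correction because the text must be rewritten anyway, and the existing text commits to separate tests at each time point with baseline among them.

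**Conclusion.** The point holds as a conflict within the current text. The Data Analysis section counts 3 time points, and the current schedule implies 2. For each outcome, one planned time point should have no data, one is baseline, and one comparison bears on the effect of the intervention.

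This rests on three assumptions: that the initial assessment is the baseline, that the current schedule has a single reassessment, and that this reassessment is the 6-month one. The Reassessments section gives 6 months as an outer limit and as the reason for the change.

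A reader might infer more than the article supports:

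- *That the planned analysis cannot be run.* Only the part at the third time point lacks data. The groups can still be compared at 6 months.
- *That 3-month data will be used selectively.* This would require such data to exist. The article gives neither the date of the deviation nor any sign that a participant was seen at month 3.
- *That 30 tests inflate the error rate.* The figure depends on the assumption of one test per instrument per time point. Ten of those tests should have no data, and ten at baseline support no claim of effect. It shows how far the text departs from the design and does not measure bias.
- *That the registry entry is wrong.* It is not among the documents, so whether it needs changing cannot be judged.

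**What to change.** Reconcile the Data Analysis section with the Reassessments section:

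1. Replace the two references to three time points with two named ones: baseline and the 6-month reassessment.
2. Make the between-group difference at 6 months, adjusted for the baseline score, the single test of effect for each outcome.
3. Present baseline by group descriptively, without P values.
4. State whether any 3-month assessments were done before the deviation was adopted. If so, give the number per arm and report them descriptively only.

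The cost is a revision of one section and a sentence on the deviation. Item 4 needs a look at the trial's own records but no new measurements. Baseline adjustment uses scores that the design already provides. As the analysis was under way when the article was written, the correction should be made, and its date recorded, before the results are published.
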